**2. THE PROPOSED TRIAL**

**2.1 What is the proposed trial design?**

A single-centre, randomized, factorial (2x2), controlled, pilot trial. Children aged 3-60 months admitted to the paediatric ward of the Princess Marina Hospital in Gaborone, Botswana, with acute non-dysenteric diarrhoeal disease will be randomized to one of four arms: rapid stool testing/targeted antimicrobial therapy plus probiotic treatment, rapid stool testing/targeted antimicrobial therapy plus placebo treatment, delayed stool testing plus probiotic treatment, or delayed stool testing plus placebo treatment. The primary outcome is 60-day mortality. See Appendix 1 for flowchart of study procedures.

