**1.2 What are the principal research questions to be addressed?**

Our research question is whether, in children under five years of age admitted to hospital because of acute non-dysenteric diarrhoeal disease, rapid testing of stools for treatable bacterial/parasitic pathogens – accompanied by prompt treatment of these pathogens if detected – plus treatment with *Lactobacillus GG***,** will lead to decreased mortality and stunting at 60 days. Testing this hypothesis will likely require a large multicentre randomized trial, so we propose to first conduct a **pilot** **whose goal will be to demonstrate feasibility**. The specific feasibility criteria of this pilot are:

1) to enroll at least 100 participants during the 12-month study period;

2) to ensure that >95% of participants have a rectal swab taken within 18 hours of admission;

3) to verify that >95% of rectal swabs in the experimental group are resulted within 48 hours of admission;

4) to ensure >95% of participants found to have a treatable enteric pathogen are prescribed appropriate antimicrobials;

5) to ensure that >95% of participants prescribed antimicrobials start them within 24 hours of the test being resulted;

6) to contact >95% of participants 7-14 days after discharge from hospital; and

7) to contact >90% of participants 60 days after admission to hospital.

All aspects of the proposed follow-up trial will be assessed, including enrolment, randomization, follow up, methods for outcome assessment, and event rates. The data collection forms and data management strategy will be tested, data to derive a precise sample size will be generated, and assumptions for a cost effectiveness analysis will be assessed.

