**1.4 How will the results of the trial be used?**

Before the widespread introduction of a new diagnostic test, there must be demonstrable benefit associated with its use; this is even more important in a setting such as sub-Saharan Africa where the public health care systems have very limited resources. Many organizations, both public and private, are spending time developing novel diagnostics – but no one has yet investigated their use in a systematic fashion within the parameters of a randomized controlled trial. The results of this trial will be of paramount importance to clinicians, patients, and health-care policy-makers in resource-limited settings.

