**2.5 What are the proposed practical arrangements for allocating participants to trial groups?**

A statistician independent of the study will generate a randomization list such that participants can be assigned at random to one of the four study groups in a 1:1:1:1 ratio. The randomization code will be generated by a random number generator and will be blocked (randomly in groups of 4-8), with the random blocking not disclosed. Given the substantial increase in mortality among children with severe acute malnutrition, randomization will be stratified by its presence or absence. Randomization will be communicated to the research assistant using an internet-based system.

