**2.8 What are the proposed *clinical* outcome measures?**

**2.8.1 Primary clinical outcome.** The primary outcome is mortality. If the participant dies prior to the 60-day followup, the research assistant will determine the date of death as accurately as possible.

**2.8.2 Other clinical outcomes.** Secondary outcomes will include the following: weight z-score at 60-day followup adjusted for initial weight; height z-score at 60-day followup adjusted for initial height; presence of stunting at 60-day followup; length of stay in hospital; number of days with at least three watery stools; number of days of fever in hospital; 7-day mortality; recurrence of acute diarrhoea during the 60-day followup period; re-presentation to a medical professional because of acute diarrhoea during the 60-day followup period; readmission to a paediatric medical ward during the 60-day followup period; HIV viral load (detectable/undetectable) at the next assessment within 6 months of enrollment, for those participants that are HIV positive; and environmental enteropathy score([21](#_ENREF_21)) (composite of faecal alpha-1 antitrypsin, neopterin, and myeloperoxidase) at 60 days.

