**2.11 What is the proposed sample size?**

For this pilot study, a sample of 100 participants will be adequate to evaluate the feasibility criteria.

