**2.13 What is the proposed type of analysis?**

The principal analysis will be intention-to-treat, i.e. all participants will be analyzed in the groups to which they were randomized, regardless if they received the appropriate antimicrobials (for those in the rapid swab analysis groups) or if they were adherent to the probiotic treatment (for those in the relevant groups). As the primary outcome (mortality) is binary, the chi-square test will be used. The chi-square test will also be used to interpret the following secondary outcomes: presence of stunting at 60-day followup, 7-day mortality, recurrence of acute diarrhoea during the 60-day followup period, re-presentation to a medical professional or readmission to Princess Marina Hospital because of acute diarrhoea in the 60-day followup period, and detectable HIV viral load within 6 months of enrollment. Analysis of covariance or logistic regression will be used to analyze the following secondary outcomes: height z-score at 60 days adjusted for initial height, weight z-score at 60 days adjusted for initial weight, and environmental enteropathy score at 60 days. Survival analysis will be used to analyze the following secondary outcomes: length of stay in hospital, number of days with at least three watery stools, and number of days of fever in hospital. Secondary analyses will attempt to control for the time to initiation of appropriate antimicrobial therapy and the time to initiation of probiotic therapy. Statistical analysis will be conducted using STATA 11.0 (College Station, TX).

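### The pilot's goal, success criteria and sample size rest on feasibility, but sections 2.1 and 2.13 make 60-day mortality the primary outcome and between-group tests the principal analysis

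*Protocol*

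**What the plan says.** Two groups of statements in the protocol point in different directions.

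**Feasibility**
- Section 1.2 describes a pilot "whose goal will be to demonstrate feasibility" and says that the mortality and stunting hypothesis will probably need a much larger trial at several centres.
- Section 2.10 lists seven feasibility targets, and its heading equates them with the pilot's criteria for success.
- Section 2.11 gives the only sample-size justification: "For this pilot study, a sample of 100 participants will be adequate to evaluate the feasibility criteria".

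**Efficacy**
- Section 2.1: "The primary outcome is 60-day mortality". Nothing there limits this to the clinical side of the study.
- Section 2.8.1: "The primary outcome is mortality", here under a heading that adds the word *clinical*.
- Sections 2.3 and 2.7 also call the 60-day (2-month) assessment the measurement of the primary outcome.
- Section 2.13: "The principal analysis will be intention-to-treat, i.e. all participants will be analyzed in the groups to which they were randomized", followed by "As the primary outcome (mortality) is binary, the chi-square test will be used". It then assigns chi-square tests, analysis of covariance or logistic regression, and survival analysis to the secondary clinical outcomes. It does not mention the seven criteria.

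**The concern.** A trial's primary outcome and principal analysis tell the reader which result answers its question. Here the question and the sample size concern feasibility, while the outcome called primary and the analysis called principal concern efficacy. Anyone who follows 2.1 and 2.13 would lead the report with a mortality p-value from about 100 children.

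Two misreadings are at stake. A non-significant mortality comparison could be taken as evidence of no benefit when the study could hardly have shown any. A nominally significant result among the secondary outcomes could be taken as a signal when it may be chance. Section 1.2 intends the pilot's data to inform the main trial's sample size, so neither misreading would be harmless.

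**Working it through.** The protocol gives no alpha, power, effect size or precision target for its 100 children, so there is no figure to reproduce. The check asks what 100 children can do for each of the two purposes.

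**Inputs**
- Total 100 (2.11). Participants are "assigned at random to one of the four study groups in a 1:1:1:1 ratio" (2.5), so about 25 per cell and 50 v 50 for each factor. The probiotic factor has fewer, because children with severe acute malnutrition are not randomized to it (2.2.1).
- Control mortality 3.2%, the only overall rate in the document (1.1). It comes from an external study of moderate-to-severe diarrhoea, so it is an assumption here. Range examined: 3.2% to 15%.
- Two-sided 5% and the effect sizes are assumptions. Losses (fewer than 5 expected, 2.12) are ignored.

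**Mortality test**

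Expected deaths with no effect: 100 × 0.032 = 3.2.

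Uncorrected chi-square = N(ad − bc)² / (product of the four margins). With no deaths in one group of 50:
- 3 v 0: 100 × (3 × 50)² / (50 × 50 × 3 × 97) = 3.09, p = 0.079.
- 4 v 0: 100 × (4 × 50)² / (50 × 50 × 4 × 96) = 4.17, p = 0.041.

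Significance therefore needs at least four deaths against none, when about three are expected in total. Fisher's exact test would need 6 v 0 (p = 0.027).

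Exact power is the sum of the two-binomial probabilities over all tables with p < 0.05, with 50 per group:

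| Control mortality | Halved | Reduced by 75% | All deaths prevented |
|---|---|---|---|
| 3.2% | 3.6% | 5.1% | 7.6% |
| 5% | 7.5% | 13.2% | 24.0% |
| 10% | 14.5% | 32.5% | 75.0% |
| 15% | 22.6% | 50.4% | 95.4% |

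At 3.2% with no effect at all, the test rejects 3.1% of the time, so it hardly separates a halving from nothing. By the normal approximation, 80% power for a halving from 3.2% needs about 1,436 children per group.

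**Chance findings among secondary outcomes**

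Section 2.8.2 lists 12 secondary outcomes. Section 2.13 gives 11, because it merges re-presentation and readmission. With no true effects and independent tests at 5%, the chance of at least one false positive is 1 − 0.95^k:
- One factor: k = 11 gives 43%; k = 12 gives 46%.
- Both factors: k = 22 gives 68%; k = 24 gives 71%.

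These are upper figures. Correlated outcomes lower them, as do sparse ones such as 7-day mortality.

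**Feasibility**

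Exact (Clopper-Pearson) 95% intervals:
- 96/100: 90.1% to 98.9%.
- 91/100: 83.6% to 95.8%.
- 48/50 (a criterion that applies to the rapid-testing arms only): 86.3% to 99.5%.

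The sample gives usable estimates for the feasibility criteria and almost no information on mortality.

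**The case against.** The protocol can be read as running two labelled tracks. Sections 2.8 and 2.9 are headed as clinical outcomes, 2.8.1 as the primary clinical outcome, and 2.10 as the feasibility outcomes that define success. Carrying the main trial's outcomes is deliberate, since 1.2 wants outcome assessment and event rates tried out. This stands in part: it softens the conflict. It does not remove it, because 2.1 and 2.13 drop the distinction, and those are the sections that fix the primary outcome and the principal analysis.

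Several stronger readings are tempting, and the document does not support them:
- *The mortality test cannot succeed.* Too strong. Power is low for realistic effects, but at 10% mortality it is 75% if every death is prevented. Sections 2.5 and 2.14 say that mortality is much higher in severe acute malnutrition, and those children are eligible.
- *The pilot's formal result is a mortality p-value, which would decide the main trial.* Section 2.10 ties success to feasibility, and no section ties progression or choice of arm to a p-value.
- *A chance-positive secondary result is likely.* With independent tests the chance passes one half only if both factors are tested on essentially all outcomes at an assumed 5%.
- *The missing multiplicity rule is itself a defect.* Such a rule may be in a statistical analysis plan that is not shown, and so may the detailed analysis of the seven criteria. The point made here is only about which outcome is called primary and which analysis principal, which the protocol itself fixes.
- *Section 1.4 overclaims.* It says "The results of this trial will be of paramount importance to clinicians, patients, and health-care policy-makers in resource-limited settings", but in the setting of a general rationale for evaluating diagnostics. It does not say that the pilot's clinical tests will be conclusive, so rewriting it is a matter of preference.

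**Conclusion.** The inconsistency is real and lies in the text. Sections 1.2, 2.10 and 2.11 rest on feasibility, whereas 2.1 names mortality as primary without qualification and 2.13 makes between-group tests the principal analysis. For a halving of mortality, power runs from 3.6% to 22.6% as control mortality goes from 3.2% to 15%, so a null result would carry almost no information about benefit. This rests on 50 v 50, the uncorrected chi-square test and a two-sided 5% level that the protocol does not state. The false-positive figures of up to 46% (one factor) and 71% (both) also assume independent tests. The sections should be reconciled before results are reported, but the problem is one of labelling and role and does not invalidate the design.

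**What to change.** - **2.1 and 2.13:** name the seven feasibility criteria as the pilot's primary outcomes. Report each proportion against its stated threshold with an exact 95% interval, and enrolment as a count against 100.
- **2.1 and 2.8.1:** call 60-day mortality the primary clinical outcome intended for the main trial.
- **2.13:** keep analysis by randomized group, but report mortality and the other clinical outcomes as estimates with 95% intervals, labelled exploratory and not a basis for claiming benefit or lack of benefit.

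The cost is a change of protocol wording, with no added patients, visits or data. The downside is that clinical p-values lose any confirmatory role.

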**2.2 What is the population under study?**

**2.2.1 Inclusion criteria.**

Children aged 3 to 60 months admitted to the Princess Marina Hospital paediatric medical ward primarily because of acute diarrhoeal disease will be eligible. Acute diarrhoeal disease will be defined as at least three watery stools in the 24 hours preceding admission to hospital. Children with HIV infection will not be excluded. Children with severe acute malnutrition will be eligible to be included in the rapid vs delayed testing and targeted treatment arms, but will not be randomized to probiotic (or placebo).

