Probiotic therapy – the administration of ‘good’ bacteria – also holds promise for the supportive treatment of children with infectious gastroenteritis. A Cochrane review pooled data from 63 studies of proven or presumed infectious acute diarrhoeal disease (n=8014) and found that probiotic treatment decreased duration of diarrhoea by a mean of 24.5 hours (95% CI 16-34 h) and reduced stool frequency on day 2 of illness by a mean of 0.8 stools (95% 0.5-1.1 stools) in infants and young children, though many different probiotic preparations were used ([18](#_ENREF_18)). Almost as importantly, no significant or serious adverse reactions were found in all of these children. The majority of these studies were done in children with viral gastroenteritis, and there is no substantial evidence supporting the use of probiotics in children with bacterial or protozoal enteritis; however, it must be noted that these studies did not use advanced molecular diagnostics, and so it is very possible that many of these children had unrecognized bacterial co-infections. Another Cochrane systematic review has demonstrated that probiotic therapies can prevent paediatric antibiotic-associated diarrhoea when administered concurrently with antibiotics, suggesting that concomitant administration of antibacterials will not necessarily render the probiotics inactive ([19](#_ENREF_19)). Overall, there is a rational basis for exploring the use of probiotics in the sub-Saharan context for the treatment of infectious enteritis, whether viral, bacterial or protozoan.

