**2.2.2 Exclusion criteria.**

Children will be excluded if they have any of the following:

a) visibly bloody diarrhoea by history or at presentation, or

b) diarrhoea for > 14 days prior to admission to hospital, or

c) known inflammatory bowel disease, cystic fibrosis, or malignancy, or

d) suspected bacterial sepsis or meningitis leading to the initiation of ceftriaxone, or

e) severe metabolic acidosis with pH<7.1 or HCO3 < 10, or

f) suspected primary urinary tract infection and a urinalysis showing pyuria or positive nitrites, or

g) suspected primary diagnosis of pneumonia with a chest x-ray showing a focal consolidative process, or

h) live in a household with another individual documented to have an enteric infection of defined aetiology, or

i) are transferred from another health centre with treatment already begun with nalidixic acid, cefotaxime, or ciprofloxacin.

Children will also be excluded if they live outside Gaborone/Tlokweng/Mmopane, if they do not have a permanent address, and if a caregiver does not have ready access to a telephone (landline or mobile). We will not be enrolling children admitted to hospital for another reason who develop nosocomial diarrhoea > 48 h subsequent to enrollment. Children who require admission to hospital because of acute diarrhoeal disease who previously had been participants will not be eligible for participation again.

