**2.3.3 Delayed swab testing plus probiotic therapy arm.** These participants will be started on *Lactobacillus reuteri* within 24 hours of enrollment. Rectal swabs taken from children in the ‘delayed swab result’ arms will be batched and processed after all enrollment has been completed, and management in hospital will be at the discretion of the attending physician following Princess Marina Hospital standards of care. Should the attending physician consider the diagnosis of bacterial enteritis or cryptosporidiosis based on clinical judgment, azithromycin and/or nitazoxanide will be made available. Probiotic therapy will be continued until the measurement of the primary outcome, 2 months post-enrollment.

**2.3.4 Delayed swab testing plus placebo therapy arm.** These participants will be started on placebo therapy within 24 hours of enrollment and will have rectal swabs resulted only after the conclusion of the study (see 2.3.3). Should the attending physician consider the diagnosis of bacterial enteritis or cryptosporidiosis based on clinical judgment, azithromycin and/or nitazoxanide will be made available. Placebo therapy will be continued until the measurement of the primary outcome, 2 months post-enrollment.

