**2.4 Laboratory testing.** A flocked rectal swab (Copan Italia S.P.A, Brescia, Italy) will be used to acquire specimens from all study participants; these will be placed in vials containing ENAT medium (Copan Italia S.P.A.) for stabilization and transport. A stool sample will be taken from each participant (as soon as reasonably possible) and stored at -70C at the National Microbiology Laboratory; these will then be batched and sent to McMaster for assessment of faecal calprotectin levels. An aliquot of the ENAT medium will have DNA extracted using QIAgen total nucleic acid extraction columns and the extracted DNA will be subjected to amplification and detection using multiplex taqman assays targeting *Shigella* spp., *Campylobacter* spp., *Salmonella* spp., ETEC and *Cryptosporidium* spp. previously adapted by our group for use on the ABI 7500 Realtime FAST qPCR platform. The remainder of laboratory testing that is required (eg. verification of HIV status, if applicable) will be done as per current Princess Marina Hospital standards of care. A stool sample will be obtained at the 2-month follow-up visit that will be sent to McMaster for faecal enzyme measurement and calculation of the environmental enteropathy score (composite of faecal alpha-1 antitrypsin, neopterin, and myeloperoxidase).

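### The immune-competence ground that keeps severely malnourished children off the live probiotic is not applied to other children with severe immune suppression already known at enrollment

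*Protocol*

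**What the plan says.** Section 2.16.1 describes the probiotic as live bacteria and notes that it is not standard care for gastroenteritis in Botswana. It cites an absence of significant adverse reactions in thousands of immunocompetent children. It then reasons that children with SAM lack functional immune competence and are for that reason ineligible for probiotic. Section 2.14 again describes children with SAM as immune compromised.

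Section 2.2.1 puts this into effect. Children with SAM may enter the rapid versus delayed testing comparison, "but will not be randomized to probiotic (or placebo". The sentence just before that rule reads "Children with HIV infection will not be excluded", with no condition on disease stage, immune status or treatment.

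The closest item in section 2.2.2 is exclusion (c): "known inflammatory bowel disease, cystic fibrosis, or malignancy". It removes those children from the whole trial and gives no immune reason.

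In the probiotic arms of section 2.3, "Probiotic therapy will be continued until the measurement of the primary outcome, 2 months post-enrollment". Under section 2.5, participants are "assigned at random to one of the four study groups in a 1:1:1:1 ratio", and the only stratification factor is SAM: "randomization will be stratified by its presence or absence".

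**The concern.** The protocol treats poor immune function as sufficient reason to withhold a live organism from one group of children. The same reason appears to cover a child without SAM who is known to be severely immune suppressed, for example through advanced HIV disease, a known primary immunodeficiency or immunosuppressive treatment. That child is nevertheless eligible for probiotic under the same rules as a well-nourished, immunocompetent child, and no explanation is given.

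What is at stake is participant protection and the coherence of the risk section that ethics boards and caregivers rely on. The feasibility criteria in section 2.10 and the analyses in section 2.13 do not depend on it.

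**Working it through.** No figure in the protocol bears on this point, so the check sets the relevant sections side by side.

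1. **The ground.** Section 2.16.1 links the SAM bar causally to lack of immune competence. It follows directly on a safety statement about immunocompetent children, so immune competence is the stated reason for the bar.

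2. **Who the bar reaches.** In section 2.2.1, SAM is the only condition that takes a child out of the probiotic/placebo randomisation while leaving the child in the trial.

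3. **Who the exclusions reach.** In section 2.2.2, item (c) covers malignancy, one common setting for immune suppression. Item (d) removes suspected sepsis or meningitis for which ceftriaxone was started, and items (e) to (g) concern the acute presentation. None of the items refers to underlying immune deficiency or immunosuppressive treatment.

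4. **Any later check.** The arm descriptions in section 2.3 place no immune-status condition on starting the probiotic or on continuing it for two months.

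5. **Whether the group could arise.** HIV-infected children are expected: section 2.8.2 lists viral load as a secondary outcome for them, and section 2.14 plans to explore the effect of HIV infection or exposure. The protocol does not say how many would be severely suppressed. Primary immunodeficiency and immunosuppressive treatment are not mentioned anywhere.

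6. **Chance of exposure for one such child.** Two of the four arms contain probiotic and allocation is 1:1:1:1, so the chance is 2/4 = 1/2. This is a chance of receiving the product, not of harm. An expected count would need the number of such children, which the protocol does not give, so none is offered.

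7. **Whether the general safety statement closes the gap.** Section 1.1 reports that across 63 studies (n = 8014) "no significant or serious adverse reactions were found in all of these children". It does not state those children's immune status, so it neither shows nor rules out safety in severely suppressed children.

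Steps 1 to 4 leave one route uncovered: a child without SAM or malignancy, with severe immune suppression already on the chart, may be randomised to the live product. Nothing in the text closes or explains that route.

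**The case against.** The strongest reply is that nothing here is misstated and no two sentences collide. Section 2.16.1 gives a reason for one group; it does not lay down a rule for every immune-suppressed child. SAM is also set apart on other grounds: higher mortality (sections 2.5 and 2.14) and an exception to the usual practice on antimicrobials at admission (section 2.3.1). This stands in part. The general rule is inferred from a single group, which is a reason to call the point minor. But section 2.16.1 rests the probiotic bar on immune competence, not on mortality or antimicrobial practice, so the question of why it stops at SAM remains.

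A second reply is that the exclusions narrow the gap, and that a suppressed child who also has SAM is already covered. That is correct, and the remaining group may be empty.

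A third is that HIV-infected children are wanted in the trial. They are, but so are children with SAM, who are enrolled and kept off the probiotic. The same route serves both aims.

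A reader might infer three stronger things that the protocol does not support:

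- **That HIV-infected children should be excluded, or kept off probiotic as a group.** Their inclusion is deliberate, and HIV infection alone is not severe immune suppression.
- **That the trial exposes children to a known hazard.** The protocol contains no evidence of harm from the probiotic in any group.
- **That the cited safety evidence comes only from immunocompetent children.** Section 2.16.1 says no reactions were seen in such children; it does not say that no others were studied.

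**Conclusion.** The point holds as a minor participant-safety inconsistency. The reason given for withholding the live probiotic from children with SAM is not carried over to other children whose severe immune suppression is already known at enrollment, and no reason is given for the difference.

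Its size cannot be stated as a number. The conclusion rests on reading the causal link in section 2.16.1 as a ground that would apply equally to a comparable child. It does not rest on any estimate of risk or on what the cited studies contain. Eligibility for a study product is a protocol matter, so a statistical analysis plan would not be expected to settle it.

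**What to change.** - **Section 2.2.1:** extend the SAM testing-only route to children with severe immune suppression documented in the routine chart at enrollment. They would be randomised to rapid or delayed testing, without probiotic or placebo. The study clinicians and ethics boards should fix a simple chart-based threshold before enrollment starts.
- **Section 2.16.1:** name this group beside SAM as ineligible for probiotic.
- **Allocation:** use the same testing-only procedure as for SAM, with a conforming phrase in section 2.5. No separate list is needed. Record the reason for the testing-only route for each child, so that the SAM subgroup in section 2.14 stays identifiable.
- **No added test:** section 2.4 already leaves "verification of HIV status, if applicable" to hospital standards of care. Suppression not known at enrollment would still be missed, which is an accepted limit.

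HIV-infected children without such suppression stay in the probiotic comparison.

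The cost is a short amendment and agreement on the threshold. The probiotic comparison loses the affected children, probably few, and will not inform on severely suppressed HIV-infected children, which slightly narrows the HIV exploration in section 2.14. The testing comparison loses no one.
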